#### Association with symptom change

Overall, our preliminary findings suggest that the worksheet scores were uniquely associated with subsequent symptom change, but client skill was not. Additionally, our preliminary work indicated that symptoms do not predict the quality of worksheets completed in session, although they did predict the quality of worksheets done for homework without clinician guidance [40].

#### Relative advantage

Raters recorded the time to complete ratings (one or more worksheet per session). The mean was 7.04 min (SD = 3.90). Observation and rating of a full session requires 60–75 min or more per session, meaning that this strategy requires approximately 10% of the time required for “gold standard” ratings. The measure had good face validity, and raters viewed worksheets as moderately easy to rate.

## Methods

### CBT worksheet scoring development

Following an iterative process used in previous study, the team’s subject matter experts (who have knowledge of both CBT and the systems in which it is implemented) will develop and refine the scoring system developed in the preliminary study to generalize to common CBT worksheets, with input from end-users (e.g., clinicians, administrators, policymakers, supervisors). We will collect CBT worksheets that are distributed by large mental health systems and CBT training programs and publicly or commercially available books and manuals to identify common elements of CBT worksheets. We will use a rational approach to measure construction and refinement [41, 42], following methods outlined by Vogt and colleagues [35, 43]. We will create a brief, content-saturated measure of CBT quality, with conceptually distinct CBT domains.

We anticipate that minimal changes will be required to make the scoring system developed in the preliminary study applicable to CBT worksheets related to cognitive restructuring, given their similarity to CPT worksheets. Nearly all worksheets that focus on cognitive restructuring contain the following elements: identification of a situation, thought, and feeling/response, questions to challenge beliefs (e.g., evidence for and against), maladaptive thinking patterns, a new/balanced belief, and intensity rating of the emotions and beliefs before and after the cognitive restructuring process. We will develop scoring for common elements of worksheets that track or plan situations, behaviors, emotions, thoughts, and associated intensity ratings.

During the development phase, we will use worksheets collected in previous research. Our team will score these worksheets, and end-users (e.g., clinicians, CBT trainers, quality monitors, administrators, supervisors) will provide feedback on clarity of items, scoring rules, and ease of use, which will help us refine the measure.

Only worksheets that were completed or reviewed and refined in session will be scored to assess CBT quality. Raters will choose items from a list of domains that reflect the instructions and questions on the worksheet to be rated. Items will be scored on a Likert-type scale, and a mean score will be calculated based on all applicable worksheet items. Session scores will be a mean of all worksheets that were completed in session.

We will next examine test-retest reliability, rater agreement on the measure, and the correlation between worksheet ratings and observer ratings of fidelity. We will conduct preliminary analyses to assess associations with symptom change. As we refine the measure and identify content domains, items with higher item-total correlations will take precedence over those with lower item-total correlations, and we will take user feedback into account as well as we refine the measure before entering the validation phase.

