#### Factor analysis

We will conduct an exploratory factor analysis to examine the factor structure of items within each worksheet. It is possible that quality may differ across different elements/domains of CBT, but it is also possible that CBT quality is better represented as a composite variable (some areas are of higher quality than others and that summing across them still provides good information about overall quality). Thus, we will explore the possibility of multiple factors or domains (e.g., cognitive restructuring), and will also evaluate the extent to which the components are best represented as a latent variable, that is, a general tendency to provide high-quality CBT that is reflected in high scores across different CBT components.

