The next multi-level regression analyses will examine the session-by-session associations between quality and symptoms. Lagged multivariate models will allow for the inclusion of two outcomes (quality and symptom change) in the same model [78–80]. Evaluation of the cross-lagged paths will provide information about temporal precedence in the relationship between the two variables across time. We will also account for overall increases and decreases in the model by including time as a predictor of each outcome.

We will next determine whether the different quality measures or worksheet formats differ in terms of how strongly they are associated with subsequent symptom change. Since clients will be randomized into worksheet format (app vs paper form), a dichotomous variable with paper form as the reference will be entered at Level-2 in the analyses described above to examine whether format predicts symptom change. We will explore potential interactions with target problem (PTSD, depression, anxiety). We will examine and compare the effect sizes and the proportion of variance accounted for by the worksheet measure and the adherence checklist. We will also compare them for app vs. paper form worksheets. A medium or large effect would be clinically meaningful in the context of the pragmatic goals of this project, particularly because the reliable change index for each of our outcome measures corresponds to a large effect size [48, 49, 58]. On the other hand, if associations with outcomes differ only slightly, we would recommend selection of a quality assessment strategy based on specific programs’ needs or goals.

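### The raw-mean session score is comparable across worksheet types only if items are equally hard, and the stated primary model has no target-problem term to block the resulting confounding route

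*Protocol article*

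**What the plan says.** The rule is in the protocol article, under CBT worksheet scoring development. Item choice depends on the sheet: "Raters will choose items from a list of domains that reflect the instructions and questions on the worksheet to be rated". For each sheet, and then across sheets, the rule is: "a mean score will be calculated based on all applicable worksheet items. Session scores will be a mean of all worksheets that were completed in" … . No item weights, difficulty calibration, core item set or worksheet-type adjustment is stated.

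The same section describes two kinds of sheet. Restructuring sheets contain "identification of a situation, thought, and feeling/response, questions to challenge beliefs (e.g., evidence for and against), maladaptive thinking patterns, a new/balanced belief", plus intensity ratings. For the other kind, "We will develop scoring for common elements of worksheets that track or plan situations, behaviors, emotions, thoughts, and associated intensity ratings"; no challenging or balanced-belief element is listed there.

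Under Clinical outcome predictions, quality in sessions 1–6 is the focus of the primary analyses. Under Analyses, the dependent variable is the symptom score for each client's target problem, standardised and pooled over disorders. The covariates named as examples are baseline score, setting, veteran status and client skill, followed by a general reference to other characteristics. Neither worksheet type nor target problem is named. Target problem enters later: "We will explore potential interactions with target problem (PTSD, depression, anxiety"). Separate analyses by symptom measure are planned as secondary.

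**The concern.** A mean over whichever items apply carries two things: how well the work was done, and how easy the chosen items are to score well on. Only the first is fidelity. If tracking items are easier than challenging or balanced-belief items, the session score moves with worksheet mix at unchanged skill.

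That becomes a confounding problem if worksheet mix also differs by target problem. Standardising the symptom scores puts the instruments on one scale, but it does not make symptom change equal across disorders. With no target-problem term, a disorder that uses more tracking sheets and also improves faster (or slower) would produce an association between score and outcome without any effect of quality. This score is the predictor in the analysis on which the study is powered.

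**Working it through.** The article states no figure for this rule, so there is none to reproduce. The check has two parts, and its inputs are assumed unless marked otherwise.

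**1. Does the score depend on worksheet type at fixed skill?**

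Assume a 1–5 scale (the article says only that it is Likert-type). The same clinician scores 4.0 on every easy item and 4.0 − g on every harder item. The tracking sheet has easy items only. The restructuring sheet has 4 easy and 3 harder items, an assumed split of the elements the article lists.

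- Tracking sheet = 4.00
- Restructuring sheet = (4 × 4.0 + 3 × (4.0 − g)) / 7 = 4.00 − 3g/7

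| Gap g | Tracking | Restructuring | Session with one of each |
|---|---|---|---|
| 0 | 4.00 | 4.00 | 4.00 |
| 0.5 | 4.00 | 3.79 | 3.89 |
| 1.0 | 4.00 | 3.57 | 3.79 |
| 1.5 | 4.00 | 3.36 | 3.68 |

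At g = 0 the rule does no harm. At g = 1.0 a clinician using only restructuring sheets would have to be 0.43 points better to tie with one using only tracking sheets.

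**2. How far could this distort the pooled test of quality against outcome?**

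From the article: n = 360 clients, two-sided alpha .05. Taken as 6 scored sessions per client (the article focuses on sessions 1–6). Assumed:

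- True quality has SD 1 and no effect on outcome; score noise has SD 0.5.
- Tracking items are d true-quality SDs easier.
- The three disorders are equal in size, with 20%, 70% and 50% tracking sheets.
- Mean symptom change is 0, δ and δ/2 in those disorders, in outcome SDs.
- Clients are independent.

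Steps:

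- Mean tracking share = (.20 + .70 + .50)/3 = .467; deviations −.267, .233, .033.
- Covariance of score and outcome = dδ × (.233 + .033/2)/3 = .0833 dδ.
- Variance of the share = .0422 between disorders, plus the mean of p(1 − p)/6 = .0344 within, total .0767.
- Score variance = 1 + .25 + .0767d². Outcome variance = 1 + δ²/6.
- Spurious r = .0833 dδ / √(score variance × outcome variance); z = r√357.
- False-positive rate = P(|Z + z| > 1.96), with Z standard normal.

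| d | δ | Spurious r | z | False-positive rate |
|---|---|---|---|---|
| 0.5 | 0.3 | .011 | 0.21 | .055 |
| 0.5 | 0.5 | .018 | 0.34 | .064 |
| 1 | 0.3 | .022 | 0.41 | .069 |
| 1 | 0.5 | .035 | 0.67 | .103 |
| 2 | 0.3 | .040 | 0.75 | .117 |
| 2 | 0.5 | .065 | 1.24 | .235 |

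Client-level simulations under similar assumptions agree: .05 to .07 at d = 0.5, .06 to .11 at d = 1, and .11 to about .23 at d = 2. With adjustment for target problem the rate returns to .04 to .06.

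The calculation ignores clustering and attrition. A smaller effective sample would lower z and so reduce the excess.

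**The case against.** The strongest reply is that the article gives no item difficulties, anchors or scale points. It says that scoring rules and algorithms are held in a database, which is not shown, and anchors there might equate items across sheets. This stands. A reader might infer that the same clinician does score differently by worksheet type, or that leaving out restructuring is rewarded. The article does not support either. Both need unequal difficulty, and a low score for restructuring done badly is what a quality measure should give.

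Second, domain differences are already under study. The factor-analysis section says "It is possible that quality may differ across different elements/domains of CBT" and sets out to test it. Reliability is estimated by domain, and correlations with observer ratings are planned for subscales and matching items as well as the total. This also stands, so it would be wrong to say that every validity correlation rests on the session total. These analyses could reveal the problem, but nothing states that the session score or the primary model would then change.

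Third, the by-measure analyses are planned, and the sample-size section says the sample should support separate analyses by disorder. A slope difference between disorders cannot create a quality effect within one disorder, so these would help to expose a spurious pooled result. They are secondary, however, and leave the pooled primary estimate unadjusted. The general reference to other client characteristics could admit target problem, but those covariates are placed in exploratory analyses.

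Fourth, time is a predictor of both quality and symptoms in the lagged models, which deals with a shared drift over sessions. It does not deal with differences between disorders. The randomised app-versus-paper comparison is less exposed, since content is the same in both formats.

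**Conclusion.** The point holds in conditional form. The stated rule makes session scores comparable across worksheet types only if items are equally hard, and the article neither says so nor adjusts for it. Two further conditions are needed for confounding of the primary result: worksheet mix must vary with target problem, and symptom slopes must differ between disorders. The article states neither.

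The excess of false positives is negligible at a 0.5 SD difficulty gap and modest at 1 SD. A rate near .2 needs a 2 SD gap together with a 0.5 SD difference in symptom change and the assumed 20/70/50% mix. A reader might infer that the primary result is biased; the documents show only an open route to bias. It is worth closing because the data needed are already collected.

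**What to change.** 1. Keep the raw mean of applicable items, averaged over sheets, as the primary session score. It is simple and suits the aim of a scalable measure.
2. Enter target problem and its interaction with time as fixed effects in the primary growth model.
3. Add a sensitivity analysis that adjusts for worksheet type, either with the session's worksheet mix as a covariate or with type-adjusted scores, and report it beside the raw-mean result.

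Type-centring should not be made mandatory for the primary score: it would remove true quality differences between worksheet types and make scores depend on the sample. Weighting by item count is not needed: it favours longer sheets without correcting difficulty.

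The cost is analysis-plan wording, modest extra analysis and a few degrees of freedom. With three target problems and linear time, step 2 adds 2 + 2 = 4 fixed-effect parameters. The worksheets, item scores and target problem are already part of data collection.

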### Data collection and research strategy summary

After the development of the scoring system, we will prospectively collect data in a variety of settings, with clinicians (*n* = 120) who have varying levels of experience and expertise with CBT. We will collect data on clinician, client, and organizational characteristics that may impact the assessment of psychotherapy quality. We will collect worksheets, symptom measures, clinical notes with checklists of CBT strategies embedded within them, and therapy session recordings for participating clients. They will be provided to the investigators using secure, Institutional Review Board (IRB)-approved modes of data transmission that have been used successfully in our previous research [44–47].

Participating clients will be randomized into one of two different worksheet formats—app version or paper form (content is the same, mode of completion and data transmission differs). Raters will access the copies of the worksheets, or the mobile app dashboard, and score the worksheets. Clinicians, administrators, supervisors, and clients will be interviewed to assess perceptions of the quality assessment strategies and to determine feasibility, and these data will be analyzed using qualitative strategies.

The variety of worksheets and data capture sources (apps, paper forms) will allow assessment of clinician and client preferences, the degree of detail and completion required for accurate quality assessment. This strategy will allow us to answer several questions through our statistical and qualitative analyses. Analyses will be conducted to answer questions and test hypotheses regarding (1) the reliability and factor structure of the measure, (2) associations between the quality measure and subsequent symptom change (the primary outcome), (3) the concurrent validity of the measure, (4) whether the measure performs better than adherence checklists embedded in clinical notes, (5) whether different formats (apps vs. paper forms) have different concurrent or predictive validity, and (6) the feasibility, burden, satisfaction, and time requirements for the worksheets vs. the adherence checklists.

#### Data collection

We will collect worksheets and clinical note templates (which contain adherence checklists) from clinicians who have varying degrees of CBT expertise in a variety of settings The data sets will include variability in population characteristics and clinician training/education level*.*

#### Clinician inclusion criteria

The clinician inclusion criteria are as follows: (1) be trained (workshop or web-based training and consultation) or in training for CPT for PTSD or CBT that uses worksheets, (2) anticipate at least three eligible clients, (3) be willing to record sessions and provide worksheets and symptom measures to the study, (4) have computer and Internet access, and (5) be willing to use a mobile app on a tablet or mobile device.

#### Client inclusion criteria

Eligible clients (*n* = 360) will be (1) adult outpatients (ages 18 or older), with a clinician diagnosis of primary PTSD (PTSD-Checklist-5 score of 33 or above) [48], a depressive disorder (e.g., major depressive disorder, dysthymia; Patient Health Questionnaire score of 10 or above) [49], or an anxiety disorder (Beck Anxiety Inventory score 22 or above) [50, 51]; (2) those who are willing to allow the team to collect session recordings, measures, notes, and worksheets; (3) those who are able to read and write at a 6th-grade level or above; and (4) those who are willing to engage in CBT.

#### Client exclusion criteria

The client exclusion criteria are as follows: (1) imminent risk for suicide or homicide (requiring hospitalization), (2) in need of detoxification (can be enrolled when substance abuse treatment is not the primary treatment target), (3) active psychosis or manic episode, or (4) cognitive impairments that preclude any participation in therapy.

### Procedure

#### Recruitment and informed consent

Clinicians will be recruited through previously used recruitment strategies including presentation at clinical team meetings (at participating clinics), at CBT trainings, and/or by email. Private practitioners will be targeted through emails to professional organization listservs. After the informed consent, they will complete the clinician measures. They will be provided with an iPod touch, if needed, to use the mobile app. Their clients will be recruited using strategies approved by local systems and IRBs, such as waiting room flyers, whiteboard videos, and/or clinician or intake coordinator referral. Informed consent will be completed by study staff. Clients will then be randomized into one of two worksheet completion strategies: mobile app vs. paper form. Their sessions will be audio-recorded, worksheets will be collected, and they will complete symptom measures (every session for primary problem, every fourth for additional measures) for up to 16 sessions.

#### Worksheet transmission

Clinicians will redact any potential identifiers from worksheets and indicate whether they were completed/reviewed in session or for homework. Paper worksheets will be transmitted by fax or scanned and transmitted electronically (e.g., secure email, shared network drives, and HIPAA-compliant data storage software) depending on local capacity and regulations. The mobile apps will record the scheduled session time and timestamp the worksheets to allow discernment of whether worksheets were done in session. We will use Qualtrics to develop app-based standard cognitive and behavioral worksheets used for depression, anxiety, and PTSD. We will only score worksheets that are done in session to measure quality; scoring of worksheets that are completed for homework will be used to covary client skill in analyses.

#### Collection of adherence checklists

Because templated clinical notes that include checklists of CBT strategies are mandated in some systems and because an alternative hypothesis is that such notes may be an even more feasible, lower-burden strategy for assessing quality, particularly when notes are electronic, we will also collect clinical notes. If extraction from medical records is not possible, copies will be collected in the same way as the paper worksheets and/or using Qualtrics.

#### Collection of session audio

Sessions will be digitally recorded and uploaded to secure servers and HIPAA-compliant data software systems. These strategies have been successful in our previous research, in which over 600 clinicians have provided sessions for full CPT and CBT protocols [45, 52–54]. Clinicians provided similar data when originally trained in the treatments [3, 55, 56].

#### Incentives and retention

Clinicians will receive their worksheet ratings at the end of the study; these will include text with bullet-pointed suggestions for improvement. Clinic-level incentives such a breakfast or lunch tray will be provided once per year, if clinicians keep up with benchmarks for providing data (e.g., 85 + % of required data for currently enrolled clients). If their organization permits, they will receive a gift card for the time they spend transmitting client data (e.g., session recordings, worksheets, symptom measures) for each client. Clients will receive a gift card, if they complete at least four sessions and complete their measures for these sessions.

### Measures and assessment strategy

#### Outcomes and potential mediators

Clients will complete the measure for their primary problem/disorder each session (standard CBT practice). Clients with depression disorder will complete the Patient Health Questionnaire-9 (PHQ-9); clients with anxiety will complete the Beck Anxiety Inventory (BAI) each session, and clients with PTSD will complete the PTSD checklist-5 (PCL-5) every session [48, 57, 58]. We will standardize scores when examining outcomes for analyses but will also look separately at depression, anxiety, and PTSD outcomes in our analyses. Depression, anxiety (PHQ-9 and/or BAI, when not the primary target for treatment), and functioning (Brief Inventory for Psychosocial Functioning; B-IPF) [59] will be measured at the fourth session and posttreatment.

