#### Analyses

We will first examine distribution of key variables for skewness, variability, and outliers and apply appropriate transformation or other strategies to address non-normality (e.g., robust estimation procedures) as necessary. Symptom scores from instruments that reflect the target problem for each client (e.g., depression, anxiety, or PTSD) will be standardized, and the standard scores will be used as the dependent variable (DV). We will also conduct secondary analyses with the measures for each target problem and with the functioning measure as DVs. The study will produce hierarchical data with repeated measures (Level-1) nested within clients (Level-2) nested within clinicians (Level-3). To evaluate change in client outcomes, we will conducted multilevel regression (i.e., mixed-effects regression, hierarchical linear modeling) growth curve analysis, which offers numerous strengths for analyzing change in nested data, including efficiency in handling missing data, powerful and accurate estimation procedures adjusting for clustering, and modeling flexibility (e.g., allows for the inclusion of continuous or categorical, time-invariant or time-varying covariates and predictors). We will employ strategies to check the sensitivity of analysis results due to missing data (e.g., pattern mixture modeling) [76]. We will analyze the intent-to-treat sample [77] and completer samples. First, multiple unconditional change models (i.e., change without predictors) will be evaluated to determine the most reliable and powerful way to analyze change (e.g., linear or non-linear change; modeling time as time since baseline or as session number) and determine the most appropriate variance-covariance structure, considering, among others, the autoregressive structure.

The first set of multilevel regression analyses will evaluate trajectories of outcomes over the entire course of therapy or over the course of several sessions. We will examine the influence of potentially significant covariates (e.g., baseline scores, setting, veteran status, client skill, and other clinician, setting, or client characteristics) and include in exploratory analyses. Given the small number of systems, the system will be entered as a potential covariate to assess and adjust for its influence, but we will conduct an exploratory analysis with the system entered at Level-4.

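### The article gives two incompatible schedules for the additional measures, and under both the first functioning score comes at session 4, so the secondary functioning analysis has no pre-treatment value

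*Protocol article*

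**What the plan says.** The protocol article describes the timing of the additional measures twice.

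- **Recruitment and informed consent:** clients complete symptom measures "every session for primary problem, every fourth for additional measures) for up to 16 sessions".
- **Outcomes and potential mediators:** depression and anxiety, when not the treatment target, and "functioning (Brief Inventory for Psychosocial Functioning; B-IPF") "will be measured at the fourth session and posttreatment".

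The Analyses section then plans "secondary analyses with the measures for each target problem and with the functioning measure as DVs". The method for change is stated generally: "To evaluate change in client outcomes, we will conducted multilevel regression (i.e., mixed-effects regression, hierarchical linear modeling) growth curve analysis". The candidate forms are "linear or non-linear change; modeling time as time since baseline or as session number", and the list of covariates to be examined begins with "potentially significant covariates (e.g., baseline scores, setting, veteran status, client skill". Under Clinical outcome predictions, the primary analyses concentrate on quality in sessions 1–6.

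**The concern.** Two sections fix different occasions for the same questionnaires. They differ in number and in kind: only one names a posttreatment assessment, and only one names assessments between session 4 and the end of treatment. The article does not say which governs.

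Neither schedule includes a functioning score before treatment. The first score is taken at session 4, when some of the sessions whose quality is to be related to outcome have already taken place. If quality in those sessions affects functioning, part of the effect is already in the first score. An analysis of change from that score, or one adjusted for it, would leave that part out. This sits badly with the article's own emphasis, in the Background and under Clinical outcome predictions, on temporal precedence of quality over outcome.

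The growth-curve plan also assumes enough occasions to choose between forms of change. Under the two-occasion schedule, that choice is largely closed for functioning.

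**Working it through.** **Step 1: occasions under each schedule.** The inputs are the two schedules above. Counting every fourth session up to 16 gives sessions 4, 8, 12 and 16.

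| Sessions attended | Recruitment and informed consent | Outcomes and potential mediators |
|---|---|---|
| fewer than 4 | 0 | at most 1 (posttreatment) |
| 4 to 7 | 1 (session 4) | 2 (at exactly 4 sessions they may coincide) |
| 8 to 11 | 2 (sessions 4, 8) | 2 |
| 12 to 15 | 3 (sessions 4, 8, 12) | 2 |
| 16 | 4 (sessions 4, 8, 12, 16) | 2 |

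Neither schedule is uniformly richer. The every-fourth-session version gives more data on long courses, the other on short ones.

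**Step 2: pre-treatment functioning scores.** There are none in either column. Two other places might have supplied one. Client inclusion criteria gives entry scores only for the symptom scale of the qualifying diagnosis. The measures collected at baseline under Clinician and organization variables are clinician and organization questionnaires.

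**Step 3: what two common occasions can support.** Take sessions 4 and 16 as an example, with a linear model having a client-level random intercept (variance *a*), random slope (variance *b*), their covariance (*c*) and an independent residual (variance *s*).

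- Var at session 4 = *a* + 8*c* + 16*b* + *s*
- Var at session 16 = *a* + 32*c* + 256*b* + *s*
- Covariance = *a* + 20*c* + 64*b*

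That is three equations for four unknowns (rank 3 of 4). The variance of the difference is the sum of the two variances less twice the covariance:

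(8 + 32 − 40)*c* + (16 + 256 − 128)*b* + 2*s* = 144*b* + 2*s*

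The data therefore give this sum, but cannot divide it between slope and residual.

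For the mean, two occasions give two means. A straight line needs two coefficients and can be fitted. A quadratic needs three and cannot (rank 2 of 3).

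**Step 4: the same check with more occasions.** Sessions 4, 8 and 12 give 6 distinct moments, and sessions 4, 8, 12 and 16 give 10. In both cases the variance parameters (rank 4 of 4) and a quadratic mean (rank 3 of 3) are identified. There is still no pre-treatment value.

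**The case against.** **The article does not promise change from baseline in functioning.** It says only that functioning will be a dependent variable. Time since baseline is one example of a time axis, and baseline scores are one example of a covariate. This stands. A reader might infer that change in functioning cannot be analysed at all, but that goes too far: change from session 4 to posttreatment is estimable under the two-occasion schedule, with or without a random intercept. Random slopes and curvature are candidates in the general plan and are not specifically promised for functioning.

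**A condensed article may leave the full battery to the full protocol.** A fuller document may contain a baseline B-IPF. It could not make both stated schedules true, and the article does name specific occasions, which omit a baseline.

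**Posttreatment will not fall at one session for everyone.** Varying timing could weakly identify more of the model. That information would come from comparing clients with different lengths of treatment, and it supplies no baseline.

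Four further readings are tempting but unsupported:

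- *The missing baseline belongs to one schedule.* It arises under both; only the limit of two occasions is particular to one.
- *The 37% in the sample size section is the share of clients with no posttreatment form.* It is a combined allowance for attrition and missing data, used to set observations per client, so no count of affected clients follows from it.
- *Session 4 follows most of the quality window.* The article does not say when in the session the form is completed. If it is at the start, three of the six sessions precede it.
- *The non-target symptom scales also need a session 1 value.* No growth model of those scales is stated.

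**Conclusion.** The concern holds as a point about a secondary outcome. The two schedules cannot both be followed: they give four occasions against two for a full 16-session course, and one against two for five to seven sessions. Under either, the functioning analysis starts at session 4 and has no pre-treatment score. Under the two-occasion schedule it can estimate a linear mean change from session 4 to posttreatment. It cannot estimate non-linear change or a separable client-level random slope when the occasions are common to all clients.

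This rests on three assumptions: every fourth session is counted from session 4, the additional measures in the two sections are the same questionnaires, and residuals are independent with constant variance. The relevance of the session 1–6 window further assumes that the functioning analysis uses the same quality window as the primary analyses, which the article does not state. The primary symptom outcome is measured every session in both sections and is not affected.

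**What to change.** Reconcile Recruitment and informed consent with Outcomes and potential mediators so that both give one questionnaire schedule, including a posttreatment assessment. Add the B-IPF at consent or session 1. Then match the functioning model in Analyses to the occasions that result.

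If no baseline is added, state that the functioning analysis estimates change from session 4 only. If the two-occasion schedule is kept, limit the model to linear mean change.

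The cost is a wording change and one more brief self-report form per client at the start. A pre-treatment score cannot be recovered once a client has begun therapy, so this helps only clients not yet started.
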